#### Secondary outcome measures

i)Safety of the wards was assessed by the visiting researcher who interviewed the manager of each ward and collecting data on: number of absconsions and untoward incidents during the previous 6 months [13], proportion of patients and staff who reported being assaulted in the previous 3 months and patient and staff experience of feeling safe on the ward.ii)Service user satisfaction with care was assessed using a modified version of the Patient Satisfaction Questionnaire (PSQ) [14]. The questionnaire was modified with the approval of the team that designed the measure by changing one item to make it suitable for assessing patient experience of satisfaction with inpatient treatment (the item on “satisfaction with the place and time of the appointments” was changed to” satisfaction with the place you live” (e.g., bedroom, common areas). This questionnaire was embedded in a patient survey used in the study which included also questions on the patients’ access to community services and involvement in planning the care they receive. The patient survey was administrated by the visiting researcher on site with the help of staff members when needed to facilitate engagement with the patients.iii)Mental wellbeing of patients on wards was assessed using the Short Warwick-Edinburgh Mental Well-being Scale (SWEMWBS) [15] which was also embedded in the patient survey. The SWEMWBS was used in this study because of its brevity and robust psychometric properties [15].iv)Staff burnout was measured using the Maslach Burnout Inventory (MBI) [16, 17]. The MBI is a leading, validated measures of burnout used extensively in human services, education and business. This survey consists of 22 items that create three general subscales assessing: emotional exhaustion, depersonalization and personal accomplishment. Numerous psychometric analyses showed that the scale has both high reliability and validity as a measure of burnout [18]. The MBI was included in a staff survey used in the study which was distributed to staff to complete by the visiting researcher.v)Staff members on the ward were asked to indicate the extent to which the training and the supervision they receive was adequate to carry out their job. These questions were included in the staff survey distributed by the researcher.

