### Study procedures

#### Recruitment and consent procedures

The recruitment of the low secure units was carried out by the Quality Network for Forensic Mental Health Services team who publicised the study on the network’s website. Recruitment took place over three years as part of an annual cycle of recruitment, self-review and peer review between June 2012 and June 2014. At the beginning of each peer-review cycle, the eligible units that agreed to take part in the network were randomized to the active or control arm of the trial (see study setting and sample section for details on eligibility). Thirty-eight units in total took part in the study (75 wards). Each unit nominated a link person to communicate with the research team to arrange the data collection visit. The link person was in charge of circulating the study information sheet to staff and patients at least two weeks prior the data collection visit by the researcher and coordinate the logistic of the visit between the researcher, staff and patients on the wards. The researcher was escorted by staff members on the day of the visit to observe the wards’ facilities and complete the environmental checklist. During the escorted visit the researcher engaged with staff and patients by providing further details about the study and sought informed consent to complete the study survey from those who were willing to participate. The patients who agreed to participate were assisted by the researcher or staff to fill in their survey if needed. In order to maximize completeness of data collection, the research team made every effort to monitor participants’ retention from baseline to follow-up. Retention strategies included consistent and frequent contact of the research team with service in preparation for the data collection visits.

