#### Randomization and blinding

Some wards were part of a unit that included other wards on the same site. While there may be differences in services provided by different wards on the same unit, management is often shared and we judged that there was considerable potential for contamination of the effects of the intervention across wards on the same unit. We therefore randomized units rather than wards. The Quality Network team emailed the contact details of eligible services to an independent team based at Imperial College London which was in charge of the randomization process. This team used a web-based randomization programme and a randomization ratio of 1:1, early versus delayed participation in the network. Randomization was stratified according to the size of the unit (whether they contained up to four, or more than four wards). Following randomization of the 38 eligible units, 18 (47 %) were allocated by the independent team to the active arm and 20 (53 %) to the control arm of the study. The list of early and late participation units was then sent back to the Quality Network team that informed the units of their membership status.

Once all the units were informed of their allocation status, the quality network team sent the research team the full list of units enrolled for the study without any reference to their group membership. The research group then made contact with the units and arranged for baseline data collection. The units’ link person and all staff members were repeatedly reminded that the researcher collecting study data must not be told which arm of the trial they were in. In the event of accidental unmasking of a researcher, all further data were collected by a second researcher who was masked to the allocation status of the unit.

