#### Collection of study data

Baseline data were gathered by the researchers masked to allocation status of the units via direct observation of each individual ward and its facilities, an interview with the ward manager (to collate routine data on incidents and wards costs), and surveys of staff and service users. The unit’s link person produced a timetable for the data collection visit that specified what time and where each component of the visit would take place (e.g., managers’ interview, tour of the wards, meetings with patients and staff). All service users were asked to take part in the survey except those where clinical staff judged that their current mental state meant they should not be approached by a member of the research team. Participants were given the option of completing and returning the questionnaires on the day of the assessment or sending them back to the research team in a pre-paid envelope. Pre-paid envelopes and blank questionnaires to complete were left for those staff members that were not scheduled on shift during the visit and for service users on community leave. No identifiable information about staff and service users were recorded. Twelve months after the collection of baseline data, a member of the research team who was again masked to allocation status of the unit arranged to visit each site again for a follow-up assessment. The instruments used at baseline were administrated for a second time at follow-up in the same manner.

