#### Data management and analysis

All data were entered electronically into a database. Once data collection was completed, 100 % of the scores of the primary outcome measure were double checked against source data for accuracy. All analysis will follow the intention-to-treat principle. Descriptive analyses including tables and graphs of baseline organisational processes and clinical outcomes will be produced for each of the two arms of the trial.

The scores of the primary outcome measure (QELS checklist scores at 12 months) will be compared between the two groups using analysis of covariance (ANCOVA). The scores at 12 month will be considered as the outcome measure, with the wards’ scores at baseline used as a covariate.

The scores of the secondary outcome variables measured at the ward level and on continuous scales (e.g., number of untoward incidents), will be analysed using the unpaired *t*-test or Mann–Whitney test depending on the data distribution. Most secondary outcome variables are measured at the staff or patient level (e.g., staff burnout, service users mental wellbeing and satisfaction with care). It is anticipated that there will be clustering of outcomes as a result of participants receiving interventions on different wards. Such clustering violates the assumption that observed outcomes of participants are independent and can result in increased standard errors [20, 21]. To take account of this, these outcomes will be analysed using a two level multilevel regression models with patients/staff at level one and the wards as the second level. When measured, baseline values of each outcome will be used as a covariate in the analysis. Additional exploratory analysis will investigate possible predictors of the primary outcome (environmental checklist scores at 12 months). This analysis will be performed using multiple linear regression.

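### Ward-level incident and absconsion counts are to be compared by tests that ignore the randomised unit and, as named, leave the baseline counts unused

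*Protocol article*

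**What the plan says.** Under Secondary outcome measures, ward safety includes the "number of absconsions and untoward incidents during the previous 6 months", obtained from the ward manager. Patient and staff reports of assault and of feeling safe belong to the same outcome group.

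Under Data management and analysis, "secondary outcome variables measured at the ward level and on continuous scales (e.g., number of untoward incidents" are assigned to the unpaired t-test or Mann–Whitney test; the choice is to be made by looking at the data ("test or Mann–Whitney test depending on the data distribution"). Outcomes measured on individual patients or staff go instead to two-level models with ward as the upper level. The next sentence says that, for outcomes measured at baseline, "baseline values of each outcome will be used as a covariate in the analysis".

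Under Randomization and blinding: "We therefore randomized units rather than wards". The reason given is that "management is often shared and we judged that there was considerable potential for contamination of the effects of the intervention across wards" of one unit. Under Recruitment and consent procedures: "Thirty-eight units in total took part in the study (75 wards".

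Collection of study data states that the baseline interview with the ward manager covered incidents, and of follow-up: "The instruments used at baseline were administrated for a second time at follow-up in the same manner".

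**The concern.** The named tests take the ward as an independent observation, but allocation was made one level higher. The article's own reason for randomising units, shared management, is a reason to expect wards of a unit to resemble each other in how incidents arise and are recorded. The analysis section recognises clustering only for patients and staff within wards. If counts correlate within units, p-values for the ward-level safety comparisons are too small and confidence intervals too narrow.

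Secondly, neither test as named uses the baseline count, although it was collected and the primary ward-level outcome does receive baseline adjustment. That gives up precision.

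Thirdly, these are six-month counts treated as continuous scores. A Mann–Whitney test would give no rate ratio to report.

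Safety is the first of the secondary hypotheses, and the Discussion presents patient and staff safety as part of what is new in this trial, so a misleading p-value here would be noticed.

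**Working it through.** **Inputs from the Protocol article.** 38 units, 18 active and 20 control; 75 wards at baseline; 8 wards lost, leaving 67; randomisation stratified at up to four versus more than four wards. For the primary outcome only: difference 10, SD 13.3, baseline correlation 0.53, 5% significance, 90% power, 54 wards raised to 60.

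**Assumptions, not in the document.** The ICC between wards of a unit, the spread of unit sizes, the baseline correlation for incidents, and that the 5% level is two-sided.

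**Step 1: the plan's own figure.** No sample size is given for the ward-level secondary outcomes. The primary figure reproduces: the residual SD is 13.3 × √(1 − 0.53²) = 11.28, so n per arm = 2 × (1.960 + 1.282)² × 11.28² / 10² ≈ 26.7, rounded to 27. That gives 54 wards, and 54 / 0.9 = 60. The calculation relies on baseline adjustment and has no unit term.

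**Step 2: clustering with equal unit sizes.** Mean wards per unit m = 75/38 = 1.974. Design effect DE = 1 + (m − 1) × ICC. True two-sided error = 2 × [1 − Φ(1.96/√DE)].

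| Assumed ICC | DE | 75 wards act like | True error, 75 wards | True error, 67 wards* |
|---|---|---|---|---|
| 0.05 | 1.049 | 71.5 | 5.6% | 5.4% |
| 0.1 | 1.097 | 68.3 | 6.1% | 5.9% |
| 0.3 | 1.292 | 58.0 | 8.5% | 7.7% |
| 0.5 | 1.487 | 50.4 | 10.8% | 9.5% |

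*Assumes all 38 units still contribute, m = 67/38 = 1.763.

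**Step 3: unequal unit sizes.** For a given ICC, equal sizes are the favourable case. The stratification cut-off at four wards, against a mean of about two, suggests that uneven sizes were expected. The actual sizes are not given, so an illustrative set was used: 19 units of 1 ward, 10 of 2, 5 of 3, 2 of 4, one of 6 and one of 7. This makes 38 units and 75 wards with a coefficient of variation of 0.70. Here Σm²/Σm = 221/75 = 2.947, so DE = 1 + 1.947 × ICC. The simulation used normal outcomes, an 18:20 allocation without the size stratification, and 6,000 trials per ICC.

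| Assumed ICC | DE | Error by formula | Simulated t-test | Simulated Mann–Whitney |
|---|---|---|---|---|
| 0 | 1.00 | 5.0% | 4.8% | 4.4% |
| 0.1 | 1.19 | 7.3% | 7.5% | 7.2% |
| 0.3 | 1.58 | 11.9% | 12.1% | 11.7% |
| 0.5 | 1.97 | 16.3% | 16.8% | 16.3% |

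Mann–Whitney gives almost no protection, so choosing between the tests does not deal with the problem.

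**Step 4: unused baseline.** Adjusting for a baseline correlated at r multiplies the outcome variance by 1 − r².

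| Assumed r | Variance multiplied by | Reduction |
|---|---|---|
| 0.3 | 0.91 | 9% |
| 0.53 (primary-outcome value) | 0.72 | 28% |
| 0.7 | 0.51 | 49% |

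On the primary outcome's scale, for illustration only: without adjustment, 27 wards per arm give 10 / (13.3 × √(2/27)) = 2.76, and power Φ(2.76 − 1.96) ≈ 79% instead of 90%.

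**Step 5: the covariate sentence.** It directly follows the sentence on multilevel models for patient and staff outcomes and most naturally belongs to them. On that reading, baseline incident counts are simply not used. If it is meant to cover every outcome measured at baseline, it conflicts with the t-test and Mann–Whitney test, neither of which takes a covariate. The text does not settle which is meant.

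**The case against.** Several points can fairly be made for the plan.

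- **The inflation may be small.** There are about two wards per unit and no ICC is stated. At ICC 0.1 or below with equal sizes, the true error is at most about 6%. Nothing shows that incident counts cluster as strongly as the physical features scored by the primary checklist. This stands as a limit on size; the direction is the same for any positive ICC.
- **A reader might infer that the plan contradicts itself on baseline adjustment.** The document does not establish this, because the covariate sentence can be read as confined to the multilevel models. Its scope is unclear, no more.
- **A reader might infer that chance imbalance in ward size or baseline incidents would bias the safety result.** It would not. Under randomisation the unadjusted comparison is unbiased, and a correctly computed standard error already covers chance imbalance. The loss is precision.
- **The tests are not inherently incapable.** Either could be applied to changes from baseline, to rates per bed, or to unit-level summaries. That is correct, but the article proposes none of these. Whether counts become rates could be left to an analysis plan that is not shown. The missing unit term is different, because the article positively names an analysis of ward-level values by a two-sample test.
- **Not every safety outcome is affected.** Items reported by individual patients or staff may fall under the multilevel models. This stands.
- **The distribution-dependent choice of test does little harm to the error rate.** The simulated rates of the two tests are nearly the same. This also stands.

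**Conclusion.** The concern holds for the counts of untoward incidents and absconsions. As named, the tests treat wards as independent although units were randomised, and they leave the collected baseline counts unused.

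The true error of a nominal 5% test is about 5.6% to 10.8% for assumed ICCs of 0.05 to 0.5 with equal unit sizes, and about 7% to 17% for ICCs of 0.1 to 0.5 with the assumed uneven sizes. It would be wrong to cite 16–17% as the expected error: that needs both an ICC of 0.5 and a coefficient of variation of 0.70, and the document supports neither figure. The precision given up by ignoring baseline is between 9% and 49% of the outcome variance for r from 0.3 to 0.7, with r for incidents unknown.

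These are secondary outcomes, so the primary conclusion does not depend on this point. It should nevertheless be corrected before analysis. Whether the primary analysis needs a unit term is a separate question.

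**What to change.** Replace the t-test and Mann–Whitney test for ward-level secondary outcomes with a regression of the 12-month ward value on arm and baseline value. Include a random intercept for unit, or use unit-robust standard errors with a small-sample correction for 38 clusters. An analysis of unit-level summaries would also answer the clustering point.

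For untoward incidents and absconsions, use a count model that allows overdispersion and report a rate ratio with its confidence interval. The negative binomial is one option, not the only acceptable one. The baseline term must be defined at zero, for example log(count + 1), because some wards may have no events. Add an exposure offset only if ward size is recorded for all wards; the article does not list bed numbers among the data collected.

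State which outcomes the baseline-covariate sentence covers, and which safety items are analysed at ward level and which at individual level.

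The cost is revised analysis wording and modest extra work. The article reports data cleaning as still under way, and no new data are needed. The downsides are reliance on a model and slightly wider intervals from the clustering correction, which baseline adjustment may partly offset.

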#### Sample size

The sample size for the study was based on the primary hypothesis: the quality of the physical environment and facilities in wards that participate in the network would be higher 12 months after randomization than in those wards that do not participate in the network. A previous investigation with medium secure wards that took part in the quality network showed an increase in the proportion of standards met equivalent to a 10 % increase during the first year of membership of the network [19].

Assuming no change in outcome in the control arm, the sample size was based on detecting a 10 % difference between groups, equivalent to 10 units of the environmental checklist score. The sample size was calculated assuming an ANCOVA analysis, with the baseline scores used as the covariate. Based on preliminary data, a correlation of 0.53 between baseline and outcome scores was assumed. A standard deviation of 13.3 for the primary outcome was assumed (estimated using baseline data from the first 32 wards that took part in the trial). Using a 5 % significance level and 90 % power, it was calculated that 54 wards were required (27 in the active arm and 27 in the control arm of the trial). To take account of 10 % drop out from the study, we increased the sample size to 60 wards.

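### The two-level model for patient and staff outcomes stops at the ward and leaves out the randomised unit, so standard errors for the arm effect may be too small

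*Protocol article*

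**What the plan says.** Under Randomization and blinding, the protocol article gives its reason for cluster allocation: "management is often shared and we judged that there was considerable potential for contamination of the effects of the intervention across wards on the same" …, the last words referring to a single unit. It concludes: "We therefore randomized units rather than wards". Of the 38 units, "18 (47 %) were allocated by the independent team to the active arm and 20 (53 %) to the control arm of the study". Recruitment and consent procedures gives the total of 75 wards in those 38 units. Randomisation was stratified at four wards per unit, so units larger than that were at least foreseen.

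Under Data management and analysis, the clustering that the plan recognises is between wards: "It is anticipated that there will be clustering of outcomes as a result of participants receiving interventions on different wards". For outcomes measured on patients or staff, it then fixes the model: "these outcomes will be analysed using a two level multilevel regression models with patients/staff at level one and the wards as the second level". Baseline values enter as a covariate where they were measured. The article mentions no unit random effect, no standard error clustered on units and no unit-level analysis.

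**The concern.** Allocation varies only between units. A random intercept for ward handles the correlation of respondents within a ward, but it assumes that, given arm, two wards of one unit are no more alike than two wards of different units. The arm comparison then rests on 75 supposedly independent wards, when only 38 units were allocated independently.

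The protocol's own reason for randomising units makes zero between-unit variance a doubtful assumption for satisfaction, well-being, burnout, training and supervision, and the patient- and staff-reported parts of safety. If that variance is positive, p-values are too small and confidence intervals too narrow. The error would favour declaring an effect of network membership on outcomes that the plan describes as most of its secondary set.

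**Working it through.** **The plan's own figure.** The only calculation in the document concerns the primary outcome: "Using a 5 % significance level and 90 % power, it was calculated that 54 wards were required". With a residual SD of 13.3 × √(1 − 0.53²) = 11.28, a difference of 10 points, two-sided 5% and 90% power, it reproduces: 27 wards per arm, 54 in total, and 60 after 10% dropout. It gives no figure for patient or staff outcomes, so their error rate has to be examined under assumptions.

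**Inputs from the document.** 38 units (18 active, 20 control) and 75 wards, so 75/38 = 1.97 wards per unit on average. Not every unit can have a single ward.

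**Inputs assumed.** Variance shares for unit and ward (total variance 1), respondents per ward n, and the spread of unit sizes.

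**Formulae.** With equal n per ward, the two-level model is equivalent to a comparison of ward means that treats wards as independent.

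- Correlation of ward means within a unit: c = s²(unit) / [s²(unit) + s²(ward) + s²(residual)/n]
- Variance inflation relative to the planned model: DE = 1 + (m − 1)c, where m = Σk²/Σk and k is the number of wards in a unit
- Approximate true two-sided error rate: 2[1 − Φ(1.96/√DE)]

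**Results by formula**, with m = 1.97 (equal units) or 2.97 (illustrative unequal units):

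| Unit / ward variance | n per ward | c | DE | True error rate |
|---|---|---|---|---|
| 0.01 / 0.04 | 10 | 0.069 | 1.07–1.14 | 5.8–6.6% |
| 0.025 / 0.025 | 8–15 | 0.148–0.221 | 1.14–1.43 | 6.7–10.2% |
| 0.05 / 0.02 | 10 | 0.307 | 1.30–1.60 | 8.5–12.2% |

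Worked example for the lower end of the second row: c = 0.025/(0.025 + 0.025 + 0.95/8) = 0.148; DE = 1 + 0.97 × 0.148 = 1.14; 1.96/√1.14 ≈ 1.83, giving 6.7%.

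**Check by simulation under the null.** 8,000 runs per scenario, 38 units split 18/20, 75 wards, 10 respondents per ward, and unit plus ward variance held at 0.10. The even layout has 37 units of two wards and one of one (m = 149/75 = 1.99). The skewed layout runs from 20 single-ward units up to one of seven wards (m = 225/75 = 3.0).

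| Unit variance | Ward-level model, even | Ward-level model, skewed |
|---|---|---|
| 0 | 5.0% | 4.8% |
| 0.02 | 6.3% | 7.4% |
| 0.05 | 8.0% | 10.5% |
| 0.08 | 9.6% | 15.1% |

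In the even layout the model's mean standard error was about 0.100, against true values of 0.106, 0.113 and 0.119 for the three non-zero unit variances. A comparison of unit means held 4.6–5.1% in all eight scenarios. The 15.1% combines a skewed layout with four fifths of the cluster variance at unit level, and is best read as an outer case.

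**Loss of wards.** The abstract reports that 8 wards dropped out, leaving 67. Spread as evenly as possible over 38 units (29 of two, 9 of one), m = 125/67 = 1.87. At c = 0.25 the error rate is then 7.6%, against 7.9% for 75 wards in the even layout, so the picture hardly changes.

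**The case against.** The strongest reply is that the harm is conditional. With no between-unit variance beyond the ward there is no inflation, and the document gives no estimate of that variance. The protocol says that management is often shared, not always, and allows that services may differ between wards of one unit. Only some wards share a unit with others, and single-ward units raise no difficulty. The stated worry is contamination of the intervention effect, which supports correlation of outcomes only indirectly. All of this stands, and it limits the claim to one of plausible inflation.

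Baseline adjustment is a second mitigating factor. Because staff and patients are not linked over time, the covariate would have to be an aggregate, and it could absorb some stable unit variance. As an illustration, suppose the 0.53 correlation assumed for the primary outcome applied to the unit and ward components. It would remove 0.53² = 28% of each, so 0.025 becomes 0.018, c becomes 0.116–0.181, and the 6.7–10.2% range becomes 6.3–9.2%. The problem shrinks but does not vanish.

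Third, the ward effect already deals with clustering of respondents within wards, so the shortfall is smaller than if clustering were ignored.

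It might also be said that the levels of a model belong in the statistical analysis plan. That does not answer the point, because the article states the model and names its levels; a plan that followed it would inherit the mismatch.

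A reader might go further and infer that the standard errors are certainly too small, that wards of a unit share policies as well as management, or that the trial's main conclusion is undermined. The document supports none of these. It gives no unit-level variance, it says nothing of shared policies, and the primary outcome is analysed by a separate ANCOVA that this point does not address.

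**Conclusion.** The model as written does not match the design: units were randomised, wards are the highest level modelled, and 75 wards lie in 38 units. That mismatch is certain. Its consequence depends on between-unit variance, which the protocol's rationale makes plausible but does not quantify. Under the assumed variance shares, 8–15 respondents per ward and equal or moderately unequal unit sizes, the true type I error is roughly 6–12% against a nominal 5%. There is no inflation at zero unit variance, somewhat less where baseline adjustment absorbs unit variance, and more only in the outer case of very uneven units with most cluster variance at unit level. The point should be fixed. It does not rank higher because the inflation is moderate and this model serves secondary outcomes only.

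**What to change.** Account for the randomised unit in every patient- and staff-level analysis. Any of these would do:

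- a three-level model, with respondents within wards within units, and small-sample degrees of freedom suited to 38 clusters;
- standard errors clustered on the unit, with a small-sample correction;
- an analysis of unit-level summaries.

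With about two wards per unit and some single-ward units, the unit and ward variances may be hard to separate. The plan should say in advance that the unit effect is kept in that case and the ward effect dropped. Reporting the estimated unit-level variance would show how much the choice mattered.

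The statistical cost is slightly wider intervals; the practical cost is small apart from possible difficulty in fitting both variances. The article's status section reports data cleaning still in progress, so on that account the change could be made before analysis.

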Our primary outcome is designed to assess the quality of the physical environment and facilities on participating wards. This aspect of services is one which a previous observational study has suggested is amenable to change within the first year of participation in a quality improvement network [19]. Limitations inherent in the study design are the relatively short follow-up period and changes in patients and staff at wards that may limit our ability to assess the impact of participation in the network on patient and staff outcomes. Staff involved in setting up the network were concerned about withholding membership from control wards. Wards felt that a delay of more than a year would be unacceptable. This means that we will only be able to examine the impact of the first year of membership of the network and we will not be able to examine any benefits associated with longer-term participation. Given turnover in staff and patients at study wards, we are not able to compare changes in staff burnout, or patient mental health and satisfaction with treatment at an individual level. Whilst we will be able to explore aggregate changes in these measures, it is possible that planned changes or random variations in intake of patients will limit our ability of the study to demonstrate the impact of peer-networks on these measures.

Nonetheless, we believe that this study provides a rare opportunity to examine the impact of a peer-led quality improvement initiative on the quality of inpatient mental health services. The findings will also add to our understanding of the impact of this widely used approach to improve the quality of health services.

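### The baseline covariate for staff and patient outcomes has no stated level; read as each respondent's own baseline, it conflicts with anonymous surveys and turnover

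*Protocol article*

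**What the plan says.** The statements come from three parts of the protocol article.

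- **Data management and analysis.** "Most secondary outcome variables are measured at the staff or patient level". These outcomes go into "two level multilevel regression models with patients/staff at level one and the wards as the second level". The article then adds that, when measured, "baseline values of each outcome will be used as a covariate in the analysis". No level is named for this covariate. For the primary outcome, the same section does name the level: the ward's own checklist score at baseline.
- **Collection of study data.** "No identifiable information about staff and service users were recorded". No anonymous linkage code is described. Questionnaires could be posted back, and blank copies were left for absent staff and for service users on leave. On timing: "The instruments used at baseline were administrated for a second time at follow-up in the same manner".
- **Discussion.** Because of turnover, "we are not able to compare changes in staff burnout, or patient mental health and satisfaction with treatment at an individual level". The next sentence begins: "Whilst we will be able to explore aggregate changes in these measures".

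The Randomization and blinding section adds that units, not wards, were randomised, because wards in a unit often share management.

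**The concern.** In a regression whose outcome is one respondent's 12-month score, the baseline value of that outcome would ordinarily be taken as the same respondent's earlier score. Dropping the reference to wards that qualifies the primary-outcome covariate strengthens that reading. Yet the data collection and Discussion sections describe what are in effect repeated cross-sections of wards: whoever was there and willing at each visit, with no described way to link the two waves.

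This leaves the analyst to choose between a ward mean, a joint model of both waves and no adjustment. These give different estimates and standard errors. The Status of the trial section says that follow-up data collection had finished and cleaning was under way, so the choice could be made with the data in hand. Secondary hypotheses ii to v (satisfaction, well-being, burnout, training and supervision) all rest on survey responses, as does the experience-of-safety part of hypothesis i.

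**Working it through.** **1. The plan's own figure.** The only sample size in the article is for the primary outcome. Inputs from the Sample size section: difference 10, SD 13.3, baseline–outcome correlation 0.53, 5% significance (taken as two-sided), 90% power.

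- Residual variance: 13.3² × (1 − 0.53²) = 176.89 × 0.7191 = 127.2, so the residual SD is 11.28.
- Per arm: 2 × (1.960 + 1.282)² × 127.2 / 10² = 26.7, rounded up to 27. The total is 54.
- With 10% dropout: 54 / 0.9 = 60.

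Both stated figures reproduce. They use a ward-level baseline that exists, so this point does not touch them.

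**2. Which baseline can be used for the survey outcomes?**

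| Candidate covariate | What the article implies |
|---|---|
| Respondent's own baseline | Needs linked records; no identifiers, no code described, individual comparison ruled out |
| Ward's baseline mean | Same instruments on the same wards at both times, so it can be formed |

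The words about a covariate being measured do not settle the matter. The survey instruments were given at baseline, so the outcomes were measured; what is missing is a link to individuals.

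**3. What can the ward mean recover?** The article gives no ICC, no number of respondents per ward and no stability over time for these outcomes, so all three are assumed here. Let m be respondents per ward at each wave, and 0.8 the correlation over time of the true ward effects. Take different respondents at the two waves.

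- Reliability of a ward mean: R = m × ICC / (1 + (m − 1) × ICC).
- Correlation of baseline and follow-up ward means: r = 0.8 × R.
- Variance of the arm difference relative to no adjustment: about 1 − r².

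| ICC | m | R | r | 1 − r² |
|---|---|---|---|---|
| 0.05 | 5 | 0.208 | 0.167 | 0.972 |
| 0.05 | 10 | 0.345 | 0.276 | 0.924 |
| 0.10 | 5 | 0.357 | 0.286 | 0.918 |
| 0.10 | 10 | 0.526 | 0.421 | 0.823 |
| 0.20 | 5 | 0.556 | 0.444 | 0.802 |
| 0.20 | 10 | 0.714 | 0.571 | 0.673 |

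For example, with ICC 0.05 and m = 10: R = 0.5 / 1.45 = 0.345, r = 0.8 × 0.345 = 0.276, and 1 − 0.276² = 0.924. This approximation treats wards as independent and equal in size.

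**4. Can the model be fitted without linkage?** One simulated data set had 67 wards (75 − 8), 8 respondents per ward at each wave, ICC 0.10 and ward-level correlation 0.8. A two-level model with the ward's baseline mean as covariate fitted without difficulty. The standard error of the arm effect was 0.086 with the covariate and 0.096 without. A single data set shows feasibility only; it does not estimate the gain.

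**5. The level of randomisation.** The article has 75 wards in 38 units, or 75 / 38 = 1.97 wards per unit on average. Wards in one unit share an arm, and often management, but the stated model stops at the ward. No unit-level ICC is given, so the effect on the standard errors is not quantified here.

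**The case against.** The strongest reply is that the article never says the covariate is individual. It leaves the level open, it already uses a ward-level baseline for the primary outcome, and its Discussion points to aggregate change. Read together, the sections favour a ward summary. A condensed article may also leave such model detail to an analysis plan that is not shown.

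Much of this stands. A reader might infer that the plan specifies an individual-level covariate and that the stated model therefore cannot be fitted. The text supports neither: no level is named, and a two-level model accepts a ward-level covariate. Nor does the article prove that no respondent could be linked. Recording nothing identifiable does not strictly exclude an anonymous code, although none is described and the Discussion makes linkage unlikely. The remark on participants' retention under Recruitment and consent procedures does not show individual tracking either, since the strategy described is contact with services.

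What does not stand is that this is mere omitted detail. The article states an adjustment whose natural reading its own account of data collection and limitations rules out. That is a conflict between sections, and the published text should resolve it.

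**Conclusion.** The point holds as an ambiguity with one infeasible reading. The analysis section does not define the baseline covariate for staff and patient outcomes. Taken as the respondent's own score, it is incompatible with the data collection section and the Discussion, unless an undescribed linkage code exists.

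The consequence is moderate. It concerns secondary outcomes only. A reader might infer that the randomised comparison would be biased; it would not be by this alone, because omitting or aggregating a baseline covariate mainly costs precision. Under the assumed ranges (ICC 0.05 to 0.20, 5 to 10 respondents per ward, ward-level correlation over time 0.8), the ward mean reduces the variance of the arm difference by about 3% to 33%. At the low end the gain is slight. The firmer reason to act is to fix the model in advance and bring the sections into agreement.

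**What to change.** State that the staff and patient surveys are repeated cross-sections of wards; if an anonymous linkage code exists, describe it instead. Then specify that every 12-month respondent is analysed, with the ward's baseline mean of the same measure as a ward-level covariate and random effects for ward and for unit. The unit effect belongs there because units were randomised. A joint model of both waves is an optional check.

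The cost is a change of wording, with no new data. The drawback is that a mean of a few respondents is a noisy covariate, so the gain in precision may be small.
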